Appendix H: INFORMATION SHEET FOR PLAYERS' PARENTS OR LEGAL GUARDIANS

Appendix I: INFORMED CONSENT FORM

Appendix J: DATA ANALYSIS TABLE

Appendix K: QUESTIONNAIRE FOR COACHES

Appendix L: 11+ WARM UP EXERCISES

Appendix M: CONTENT FOR THE TRAINING

Appendix N: THE "11+" RECORDING FORM

## GLOSSARY OF TERMS

**Coach:** One who instructs players in the fundamentals of a competitive sport and directs team strategy (Merriam-Webster Online Dictionary, 2010).

**Exposure factor:** Individual participation time recorded (Hägglund, Waldén, & Ekstrand, 2006)

**Recurrent injury:** injury of the same type and at the same site which occurs after a player's return to full participation within two months (Fuller et al., 2006).

**Injury prevention:** the implementation of interventions to eliminate or reduce the likelihood and the severity of injuries caused by external or internal mechanisms before they occur (Lawrence, 2008).

**Injury severity:** Based on absence from game or practice participation: slight (1–3 days), minor (4–7 days), moderate (8–28 days), major (>28 days) (Fuller et al., 2006).

**Rehabilitation:** A player is considered injured until given clearance by medical staff to participate fully in team training and match play (Hägglund et al., 2006).

**Soccer Injury:** Any physical complaint resulted for soccer participation whether in training or match (Junge & Dvorac, 2000).

**Training session:** Coach directed physical activities (on field, gym, recovery sessions, aerobics) carried out with the team (Hägglund et al., 2006).

**Readiness for injury prevention:** Coach related factor that is assumed to influence sports injury outcomes (Siwon, 2013).

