##### **Objectives**

- a. To determine the difference in etiology, nature, severity and location of injuries between first and second division soccer players
- b. To assess whether there is any relationship between injury pattern and players' age, playing position and division of play.
- c. To determine whether nonmodifiable and modifiable intrinsic risk factors predict the risk of sustaining an injury in male soccer players in Rwanda.
- d. To assess if there is any difference in injury pattern according to training and match exposure
- e. To determine whether the availability of the medical support into the teams is associated with the incidence of re-injuries

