### **2.3.2 Objectives**

- a. To determine the difference in etiology, nature, severity and location of injuries between first and second division soccer players
- b. To assess whether there is any relationship between injury pattern and players' age, playing position and division of play.
- c. To assess if there is any difference in injury pattern according to training and match exposure
- d. To describe the availability of the medical support into the teams

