Player exposure forms will then be provided to the coaches and will be requested to record every training time that each player participate in soccer activities. Because coaches are focusing on the game during the match, it could be hectic for them to record match exposure. For this reason, match exposure will be obtained from the reports that are submitted by the referee to the FERWAFA.

Before the beginning of each season the FERWAFA set a deadline for the teams to submit the list of all the players that they will use in the league. Therefore the list of all the players will be obtained from the FERWAFA while additional information pertaining to the study will be requested from the team management.

All the medical personnel of the teams will be invited into the briefing meeting that will be held at the FERWAFA premises to explain to them about the study and their task in the study. They will be explained how to fill the injury report forms and they will be asked to report any injury that will take place during data collection. The injury report and exposure forms will be collected by the researcher or the research assistants after every two weeks.

Training and match exposure as well as injury recording for the main study will commence one week before the first game because training performed during that week is for the preparation of the first game. The first division season will start in September 2014 while the second division season will start in November 2014. The exact dates will be obtained from the FERWAFA after the general assembly meeting preparing the league that will take place after the season 2013-2014. Data collection will take place throughout the season up to the last game. Because the FERWAFA allows the teams to recruit new players during the mid season, players who will join the teams halfway through will be recorded from the period recruited. The season will end in June 2015 for the first division and May 2015 for the second division. At the end of the season, the last two teams from the first division are relegated to the second division while the first two teams in the second division are promoted to the first division. A period of rest is given to the

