### **2.3.9 Statistical analysis**

All data will be analyzed statistically using STATISTICA version 12. Standard descriptive statistics will be used for numerical variables as means, standard deviations (SD) or 95% confidence intervals (CI).

In this study incidence for all injuries will be expressed as injuries per 1000 soccer playing hours for the purpose of the comparison with previous epidemiological studies. Risk per 1000 hours of exposure either per match, training or both will be equal to number of injuries multiplied by 1000 per total exposure time. The variations of injuries during match, training or both for the two seasons will be analyzed using Analysis of Variance (ANOVA). ANOVA will also be used to analyze the occurrence of injuries according to the position in the team and division of play. The categorical variables such as the frequency, type, location, severity as well as the mechanism of injuries will be analyzed using a Chi-square test or Fisher's exact test for small numbers. Between groups incidence of injuries will be compared using z-statistics and rate ratios (RR) with a 95% CI will used to present data. The level of significance for all the tests is set to 0.05. Univariate and multivariate regression analyses will be used to calculate odds ratios (ORs) and 95% confidence intervals (CIs) for  $\pm 1$  standard deviation of change. The details of all the statistical analysis that will be performed are provided in the appendix J.

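### The chi-square and Fisher tests of injury type and location have no rule for repeated injuries in one player, so comparisons between groups of players reject more often than the stated 5%

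*Combined protocol and SAP*

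**What the plan says.** Section 2.3.9 gives the test: "The categorical variables such as the frequency, type, location, severity as well as the mechanism of injuries will be analyzed using a Chi-square test". For sparse tables it switches to the exact test of Fisher. On the error rate it adds: "The level of significance for all the tests is set to 0.05". Type and location are attributes of an injury, so the unit counted in these tables is the injury, not the player.

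The visible text points to all injuries being counted. Under 2.3.6.1, team medical personnel are told that "they will be asked to report any injury that will take place during data collection". Section 2.3.9 says that "incidence for all injuries will be expressed as injuries per 1000 soccer playing hours". Neither section excludes, separates or adjusts for recurrences, and 2.3.9 names no player-level adjustment.

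The Glossary of Terms defines a recurrent injury as "injury of the same type and at the same site", occurring within two months of return to full participation.

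Two objectives in 2.3.2 show what the tests are for. One compares groups of players: "To determine the difference in etiology, nature, severity and location of injuries between first and second division soccer players". Another compares groups of injuries: "To assess if there is any difference in injury pattern according to training and match exposure". A further objective in 2.3.2 relates injury pattern to age, position and division. Section 1.3 also lists a re-injury objective: "To determine whether the availability of the medical support into the teams is associated with the incidence of re-injuries". The plan therefore expects recurrences to occur.

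Section 2.3.9 refers to Appendix J for the details of the analysis. Appendix J is not in the text available for review.

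**The concern.** The reference distributions of the chi-square and Fisher tests assume that each injury falls into its cell independently of the others. By the plan's own definition, a re-injury cannot do so: its type and site are fixed by the first injury. In a comparison between divisions, positions or age groups, the two records belong to one player and normally sit in the same group and the same cell. The table then appears to hold more independent information than it does, and the test becomes too ready to reject. Switching to Fisher's test for small numbers does not help, because it makes the same assumption.

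At stake are the Study One objectives on injury pattern. A difference in type or location between divisions could be reported at a nominal 5% when the real error rate is higher, most of all for finely divided location tables. The problem comes from the definition of recurrence and would exist even with no correlation between players of the same team.

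**Working it through.** **Inputs**
- Nominal level: 0.05 (2.3.9).
- A recurrence has the same type and site as its first injury (Glossary).
- Proportion of first injuries that recur once, p: not given. Assumed 5-30%.
- Number of analysis categories, K: not given in the available text. Shown for K = 2, 5 and 10 with two groups, so df = K − 1.
- Both groups have the same true pattern and the same recurrence rate.

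**Variance inflation.** Each first injury contributes m records to one cell, where m = 1 with probability 1 − p and m = 2 with probability p. Then E[m] = 1 + p and E[m²] = (1 − p) + 4p = 1 + 3p, so

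D = E[m²]/E[m] = (1 + 3p)/(1 + p).

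With q = p/(1 + p), the share of all injuries that are recurrences, this is D = 1 + 2q.

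**Actual error.** The statistic behaves approximately as D times a chi-square variable, so the true rejection rate is P(χ²_df > c/D), where c is the 5% critical value. With p = 0, D = 1 and the rate is 5% for every df, which reproduces the plan's stated level.

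**Worked case.** For p = 0.15, D = 1.45/1.15 = 1.26. For K = 10, df = 9 and c = 16.92, so c/D = 13.42 and P(χ²_9 > 13.42) = 14.5%.

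| p | D | K = 2 | K = 5 | K = 10 |
|---|---|---|---|---|
| 5% | 1.10 | 6.1% | 7.0% | 7.9% |
| 10% | 1.18 | 7.1% | 9.1% | 11.2% |
| 15% | 1.26 | 8.1% | 11.1% | 14.5% |
| 20% | 1.33 | 9.0% | 13.0% | 17.7% |
| 30% | 1.46 | 10.5% | 16.5% | 23.8% |

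**Simulation check.** The check used 700 injuries, two groups of players, equal cell probabilities and 6,000 runs. The figure of 700 only sets the scale: 70% (2.4.4.3) of 990 players (2.3.4) is 693. With q = 0.20 (p = 0.25), simulated error was 10.0% for K = 2 and 20.9% for K = 10, against 9.8% and 20.9% from the formula. With no recurrences it was 4.4% to 5.3%.

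**Match versus training.** Here the two records of one player can fall on opposite sides of the comparison. If a recurrence shares the first injury's setting with probability s, and the two settings are equally common, the inflation becomes D = 1 + 2q(2s − 1).
- s = 0.5 (setting independent of the first): D = 1, so no inflation. Simulated error was 4.7% to 5.6% at every recurrence share tried.
- s = 0.75, p = 0.15: q = 0.130, D = 1.13, and the error for K = 10 is P(χ²_9 > 16.92/1.13) = 9.2%. Simulation gave 8.7%.

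**The case against.** The strongest reply is that the plan nowhere says that recurrences are counted as independent injuries. It defines recurrent injury separately, section 1.3 makes re-injury a question of its own, and the analysis details sit in Appendix J. Separate tabulation is possible. This stands as a caveat. The test that 2.3.9 names, applied to injuries reported as 2.3.6.1 asks, still leads to recurrences entering the tables, and nothing visible prevents it.

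Several stronger readings are tempting but not supported:
- **A fixed multiple.** A reader might infer that false positives are two to four times too frequent. The table runs from 1.2 times (6.1/5) to 4.8 times (23.8/5), and the documents fix neither input.
- **A 24-category location table.** Appendix B lists 24 body parts, which would give larger figures. That form records past injury history. Study injuries go on the Appendix D form, which carries its own location definitions and was not available.
- **All comparisons affected.** Match versus training shows no inflation when the recurrence's setting is independent of the first injury's.
- **Reweighting as error.** If one group has more recurrences, its all-injury pattern really is different. That is a true difference in the quantity the objective names, not a false positive.
- **Effect on the intervention.** The 11+ programme was chosen from the literature (2.2), so these tests do not select what Study Two delivers.

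It is also fair to say that testing first injuries only would change the question. The objectives ask about injuries, not first injuries.

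**Conclusion.** The concern holds for comparisons of type and location between groups of players. Followed as visible, 2.3.9 applies a test whose true error exceeds its stated 5% whenever recurrences enter as ordinary counts. The direction is certain under that condition; the size is not. Assuming that 5-30% of first injuries recur once, error is about 6-11% with 2 categories, 7-17% with 5 and 8-24% with 10. More than one recurrence per first injury would raise these figures. For match versus training the effect is conditional on setting.

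The conclusion rests on Appendix J containing no rule for repeated injuries, which could not be checked. It concerns Study One's pattern objectives, not the randomised comparison in Study Two. The change is worth making before analysis, but it does not threaten the trial's main question.

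**What to change.** In 2.3.9, keep all recorded injuries and replace the ordinary chi-square and Fisher tests of type and location with a player-clustered test: a Rao-Scott chi-square, or GEE with player as the cluster. Report a table of index injuries only as a sensitivity analysis, with re-injuries tabulated separately. If Appendix J already has such a rule, 2.3.9 need only state it.

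The clustered test should be the main analysis because it keeps the all-injury question and covers all within-player dependence. An index-only test would leave in same-site injuries that occur more than two months after return, as well as other correlation between one player's injuries.

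The cost is a few sentences in the plan, a little more analysis work and somewhat larger p-values. Players already receive identifying codes (2.3.8), so injuries can be linked to players without new data collection. Correlation within teams is a separate matter that this change does not settle.

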### **2.3.4 Participants**

The Federation of Rwandese Football Association (FERWAFA) organizes tournaments at different levels. The top flight male first division is composed of 14 teams while 19 clubs compete in the second division.

The first division competition is the country's primary soccer competition. There are 14 men's association soccer clubs that participate in the league and it operate on the process of promotion and relegation. The teams play 26 matches, where each club plays the others twice, during the season which runs from September to June. The total number of matches is 364 matches. The league is currently sponsored by the largest brewer and soft beverage company in Rwanda on its band new beer named "turbo king" and thus officially known as "turbo king national football league". At the end of the completion, the teams are ranked according to the total points accumulated during the season. In case of equal number of points the goal calculation of the number of goals scored and conceded come in favor of the team to determine the winner. The

league winner qualifies to represent the country in the CAF champions' league while the two lowest placed teams are relegated into the second division. Many teams in the first division are sponsored either by private business companies or government institutions (for example, the police, the army and other governmental parastatals) (FERWAFA, 2008).

There are 19 teams competing in the second division organized by the FERWAFA. Unlike the first division, the second division teams do not play each other because each team would play 36 games. Playing many games require many resources from the teams, the organizing federation as well as a longer period of time. Therefore the teams are randomly divided into two groups. Group A composed of 10 teams and group B composed of 9 teams. Teams in each group play each other and accumulate the points according to the win or draw rules. The first two teams in each group qualify to the semifinal stage where they play the teams from the other group. The winners of the semifinal stage qualify to the final and are automatically promoted to the first division. The competition ends while the teams play between 11 and 12 matches. The second division season runs from November to May. The FERWAFA requires each team to register maximum 30 players; therefore the maximum number of players that will participate in this study are 990.

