### **2.3.5.3 Exposure form**

A specific player exposure form developed by FIFA will be used to record detailed information regarding player involvement in soccer (Fuller et al., 2006) (Appendix C). The forms will be given to the coaches to record duration of the training sessions. Match exposure will be gathered from the referees' reports submitted to FERWAFA. Any form of physical activities supervised by the coach that the players will undertake during training will be recorded as training exposure time. Match exposure time is defined as the amount of time the player will be involved while the team is playing against another team. The duration of the training will be recorded from the start of the warm up to the end of the cool down session (Parry & Drust, 2006). Exposure form will also record player absence from training and competition and the reason for this absence. The forms will be collected by the research team once in two weeks.

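### Injury severity is an ordered scale, but the plan compares it between divisions with an unordered chi-square or Fisher test, which gives no direction or size and can cost power when severity shifts consistently

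*Combined protocol and SAP*

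**What the plan says.** The glossary grades injury severity as follows: "Based on absence from game or practice participation". The grades are slight (1 to 3 days), minor (4 to 7), moderate (8 to 28) and major (more than 28).

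Objective a of Study One, in both 1.3 and 2.3.2, is: "To determine the difference in etiology, nature, severity and location of injuries between first and second division soccer players".

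Section 2.3.9 puts severity in one list with type, location and mechanism and gives the whole list one rule: "The categorical variables such as the frequency, type, location, severity as well as the mechanism of injuries will be analyzed using a Chi-square test". When numbers are small, the plan switches to Fisher's exact test. It names no ordinal test, trend test or analysis of days absent. It promises rate ratios with 95% CIs for incidence but states no effect measure for comparing severity between divisions. It refers to Appendix J for detail; that appendix was not in the text available for this review.

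The data behind the grades are collected. Section 2.3.5.3 says: "Exposure form will also record player absence from training and competition and the reason for this absence".

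**The concern.** Type, location and mechanism have no natural order, so a chi-square test fits them. Severity has one by definition. A division-by-grade table is 2 x 4, and the chi-square test on it has 3 degrees of freedom. Its p-value is the same however the four columns are arranged, so the knowledge that major is worse than slight plays no part.

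Two things follow. First, a significant result says only that the two profiles differ. It does not say which division has the more severe injuries or by how much. Second, if the real difference is a general shift towards longer absence in one division, the test spreads its sensitivity over three directions when one matters, and is more likely to miss it.

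**Working it through.** **Plan's own figure.** There is none to reproduce. The documents give no expected number of injuries, severity distribution, target difference or power for this comparison.

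**Inputs from the documents.** Four ordered grades (glossary). Significance level 0.05 for all tests (2.3.9); sidedness is not stated, so two-sided is assumed for the 1-df test. 14 first-division and 19 second-division teams of at most 30 players (2.3.4): 14 x 30 = 420 and 19 x 30 = 570, which sum to the stated maximum of 990. The only injury frequency given is about 70% of players injured, in the Study Two sample size (2.4.4.3).

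**Step 1: 3 df against 1 df.** Suppose the whole difference lies along the ordered direction. Both tests then have the same non-centrality, (1.96 + z_power)², and differ only in degrees of freedom. For 80% power on 1 df this is (1.96 + 0.84)² = 7.85 (using unrounded z).

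| Power, ordered 1-df test | Non-centrality | Power, 3-df chi-square | Loss (points) |
|---|---|---|---|
| 20% | 1.24 | 13.3% | 6.7 |
| 40% | 2.91 | 26.7% | 13.3 |
| 60% | 4.90 | 43.2% | 16.8 |
| 70% | 6.17 | 53.1% | 16.9 |
| 80% | 7.85 | 64.5% | 15.5 |
| 90% | 10.51 | 78.4% | 11.6 |
| 95% | 12.99 | 87.1% | 7.9 |
| 99% | 18.37 | 96.3% | 2.7 |

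The loss is largest in mid-range power and fades at both ends.

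**Step 2: simulation under a consistent shift.** Assumed: independent injuries, a common odds ratio (OR) across the grade cut-points, and several grade distributions. The ordered test is the Wilcoxon rank-sum test on the grades. The counts of 294 and 399 are 70% of 420 and 70% of 570, with one injury per injured player; this is also an assumption.

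| Injuries | OR | Chi-square | Ordered test | Loss (points) |
|---|---|---|---|---|
| 100 and 100 | 1.3 | 12% | 18% | 6 |
| 147 and 200 | 1.7 | 60-61% | 76-77% | about 16 |
| 294 and 399 | 1.4 | 49-51% | 66-68% | about 17 |
| 294 and 399 | 1.5 | 67-69% | 82-83% | about 14 |
| 400 and 300 | 1.8 | 96% | 99% | 3 |
| 588 and 798 | 1.5 | 94-95% | 98-99% | about 4 |
| 400 and 300 | 2.0 | 99.3% | 99.8% | 0.5 |

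Over all scenarios with odds ratios from 1.3 to 2.0 the loss ran from about 0 to 18 points. With no true difference, both tests rejected in about 5% of runs.

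**Step 3: a difference that is not a shift.** Take grade shares of 30/25/30/15 in one division and 36/19/24/21 in the other: more slight and more major injuries together. The midrank scores from the first distribution are 0.15, 0.425, 0.70 and 0.925. The chance that an injury in the second division of the pair is graded worse (ties counted as half) is 0.36 x 0.15 + 0.19 x 0.425 + 0.24 x 0.70 + 0.21 x 0.925 = 0.497. That is almost exactly one half, so a rank test sees nothing. With 400 and 300 injuries the chi-square has 78% power and the rank test 6%. Across five non-uniform patterns the chi-square led by about 36 to 94 points.

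**The case against.** The strongest reply is that the chi-square answers the objective as written. Objective a asks whether there is a difference, with no direction, in a surveillance study with no primary severity hypothesis. The test holds its error rate for independent injuries, and a reader can see the direction in the grade percentages. This stands as far as validity goes. Percentages alone, however, give no estimate with an interval.

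A second reply is that a non-monotone pattern is conceivable here. Section 2.4.4 says second-division coaches lack the medical support of the first division and decide on return to play, and 1.1 warns that resuming play without care may aggravate injuries. Early return could add slight grades and aggravation could add major ones. This also stands, and it is a reason to keep the chi-square beside the ordered analysis.

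A third reply concerns the remedy. A plain Wilcoxon test on days absent does not allow for clustering by team. Days absent can also be cut off, because 2.3.6.1 stops data collection at the last game. And since any physical complaint counts as an injury while the lowest grade starts at one day, an analysis of days could cover a different set of injuries from the graded table. These points favour a model of the grades over a test of the days.

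Finally, Appendix J might already contain an ordered analysis. That cannot be excluded, but 2.3.9 states its rule for severity explicitly and would then have to be brought into line.

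**Conclusion.** The concern holds as a matter of efficiency and usefulness of the result. The main text applies an order-blind test to an ordered outcome named in an objective, and it plans no estimate of the difference. This part needs no assumption.

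The power cost is conditional. Under a consistent shift it is between about 0 and 18 points, and about 12 to 17 points if the ordered test would have 70% to 90% power. The range rests on assumed distributions, injury counts and odds ratios and on independent injuries. Clustering within teams and players would lower the absolute powers of both tests.

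A reader might infer three stronger things that the documents do not support:

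- That this study loses a fixed 12 to 18 points. The plan gives none of the inputs, and two seasons of follow-up with a broad injury definition could yield enough injuries to make the loss small.
- That the chi-square is invalid. It is not, for independent injuries.
- That an ordered test is always better. Step 3 of the working shows the reverse for non-monotone differences.

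**What to change.** In 2.3.9, and in any matching row of Appendix J:

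- Take severity out of the chi-square list as its main analysis. Compare the four grades between divisions with an ordinal model, for example proportional odds, with team as the cluster (GEE or a random team effect).
- Report the common odds ratio with its 95% CI.
- Keep the four-grade table by division, with the chi-square test as a stated secondary check for non-monotone differences.
- Keep chi-square or Fisher for type, location and mechanism.
- State how injuries with no day of absence are handled, since they have no grade. Define division season by season, because two teams move each way between seasons.

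The cost is a few sentences and somewhat more modelling work. No new data are needed. The authors should confirm that the named software can fit a clustered ordinal model to 33 teams. The statistical downside is low power of the ordered test against non-monotone differences, which is why the table and the chi-square stay.

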#### **2.4.3 Study design**

A cluster-randomized controlled trial will be used in this study with teams as units of randomization.

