#### **2.4.4.3 Sample size / power analysis**

Based on the study conducted by Twizere (2004), about 70% of soccer players in Rwanda sustained injuries. To obtain a 20% reduction of injuries with the implementation of the 11+ programme with the power of 90% and alpha of 5%, a sample size of 125 in each group (intervention and control) will be required. Taking into consideration the design effect of 2 for cluster randomization, the minimum number of players that should participate in this study is 217.

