#### **2.4.8 Statistical analysis**

Analysis of the incidence of injuries comparing the two study groups and the two divisions will be done as explained in the study one. Demographic characteristics of the coaches and responses on the knowledge, perception, readiness and decision making assessment will be analysed using descriptive statistics (range, mean, standard deviation). Categorical data like the coaches’ level of education, highest level of coaching license, availability of the medical personnel into the team will be presented as frequency and percentages. The five injury prevention readiness to practice questions will be coded from zero to five. The minimum score will be zero and the maximum score will be 25. The responses from the perception questions that are on a 5-point Likert scale will be recorded on a range from 1=“very unlikely” to 5=“very likely”. Therefore the results will be analysed using the descriptive statistics with means and standard deviation. Pearson correlation will be used to assess the relationship between perception variable and coaches’ readiness of sports injury prevention. The same test will be used to assess the association between readiness, perception, and first aid knowledge and compliance with the injury prevention programme. Analysis of variance test (ANOVA) will be used to analyse the difference between the coaches’ perceptions, knowledge, and readiness regarding injury prevention in the first division and the second division. The level of significance for all the tests

is set to 0.05. The details of all the statistical analysis that will be performed are provided in the appendix J.

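### Teams are randomised, but the stated between-arm test of injury incidence is a z-statistic with no named allowance for team clustering; at a variance inflation of 1.5 to 3 its nominal 5% error would be about 11% to 26%

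*Combined protocol and SAP*

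**What the plan says.** Section 2.4.3 sets the design: "A cluster-randomized controlled trial will be used in this study with teams as units of randomization". Sections 2.4.4 and 2.4.4.4 give 19 teams, split nine and ten.

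Section 2.4.4.3 recognises clustering when sizing the trial: "Taking into consideration the design effect of 2 for cluster randomization". That calculation concerns the proportion of players injured, starting from the statement that "about 70% of soccer players in Rwanda sustained injuries".

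For the analysis, section 2.4.8 states: "Analysis of the incidence of injuries comparing the two study groups and the two divisions will be done as explained in the study one". The Study One text it points to, section 2.3.9, defines incidence as "number of injuries multiplied by 1000 per total exposure time" and says that "Between groups incidence of injuries will be compared using z-statistics and rate ratios (RR) with a 95% CI". It adds: "The level of significance for all the tests is set to 0.05".

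Neither analysis section mentions teams as a source of variation. Both refer to Appendix J for details; the list of appendices calls it a data analysis table.

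**The concern.** Players in one team share a coach, training sessions and facilities. Section 2.4.4.5 says that coaches plan all activities and deliver the programme, and that one research assistant is assigned to each team. Both the true injury rate and its recording can therefore differ from team to team. One player can also contribute several injuries.

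An ordinary z-statistic for a rate ratio takes its standard error from the total number of injuries in each arm. In a team-randomised trial that standard error leaves out the between-team variation, so intervals are too narrow and p-values too small. What is at stake is objective c of Aim 2, the comparison of injury incidence between arms. The plan allows for the extra variance when it sizes the trial, but its visible analysis text does not.

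**Working it through.** **Inputs from the plan.** Design effect 2, 70% injured, a 20% reduction, 90% power, alpha 5% and 125 per group (2.4.4.3); 19 teams (2.4.4); at most 30 registered players per team (2.3.4); significance level 0.05 (2.3.9).

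**Assumptions.** The test is two-sided (not stated). The z-statistic uses the plain Poisson variance (no formula is given). The variance inflation for hourly rates is not given, so it is varied from 1.5 to 3.

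**1. The plan's own sample size.** Take the reduction as absolute, 70% to 50%, with mean proportion 0.60:

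n = [1.960 × √(2 × 0.60 × 0.40) + 1.282 × √(0.70 × 0.30 + 0.50 × 0.50)]² / 0.20² = (1.358 + 0.869)² / 0.04 ≈ 124 per group.

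The arcsine formula gives 125, so the stated figure reproduces. The total of 217 does not: 125 × 2 groups × 2 = 500. That is a separate matter. It is relevant here only because it makes the 2 a soft planning figure.

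**2. What a design effect of 2 implies.**
- For the proportion injured, DE = 1 + (m − 1) × ICC. With m = 30, ICC = 1/29 = 0.034.
- For counts, inflation = 1 + (mean injuries per team) × CV², where CV is the between-team coefficient of variation. If injuries are Poisson, 70% injured corresponds to −ln(0.30) = 1.2 injuries per player, or 36 per team of 30. A CV of 0.17 then gives 1 + 36 × 0.17² = 2.04.

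Neither value is extreme, but the documents give no estimate of either.

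**3. Error rate of the unadjusted test.** If the true variance is DE times the assumed one, the actual size is 2 × [1 − Φ(1.96/√DE)].

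| Variance inflation | 1.96/√DE | Actual two-sided error |
|---|---|---|
| 1.0 | 1.960 | 5.0% |
| 1.5 | 1.600 | 11.0% |
| 2.0 | 1.386 | 16.6% |
| 3.0 | 1.132 | 25.8% |

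At 2 the nominal 95% interval would cover about 83.4%.

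**4. Interval width at an inflation of 2.**
- Normal reference: 1/√2 = 0.71 of the correct width.
- t reference on 19 − 2 = 17 degrees of freedom: 1.96/(2.11 × 1.414) = 0.66.

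Equivalently, the unadjusted |z| would have to exceed 2.77 (normal) or 2.98 (t) to hold 5%.

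**5. Simulation check.** This used 10 against 9 teams, gamma-Poisson counts, equal exposure, no true effect and 200,000 runs. At an inflation of 2 and assumed means of 10, 21 or 30 injuries per team, the rate z-test rejected 16.2% to 16.7% of the time; a t-test on team counts rejected 4.9% to 5.0%. A z-test on the proportion injured (30 players per team, ICC 1/29) rejected 16.8%. The inflation was set by design, so this confirms the formula and says nothing about how strong clustering is in these teams.

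**The case against.** The strongest objection is Appendix J. Both analysis sections defer to it for the details, and it is not in the text available here. A reader might infer that the plan definitely ignores clustering. The documents do not support that: what can be said is that 2.3.9 and 2.4.8 name no adjustment. This stands, and it makes the point conditional. It does not remove it, because the main text names a specific test and any adjustment in the appendix would have to be reconciled with that test.

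Second, the plan nowhere says that injuries are treated as independent, and a z-statistic can be built on a robust or inflated standard error. That is true. But a z-statistic and rate ratio on injuries over total exposure, with no adjustment named, ordinarily means the simple variance.

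Third, a reader might take 17% as this trial's error rate. It is not established. The design effect was set for a proportion, no intracluster correlation is given, and the 217 does not follow from it. If 217 is read as a per-group figure, the implied inflation is 217/125 = 1.74 and the error about 13.7%. Repeat injuries could push the inflation up. The range is the proper statement.

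Fourth, a reader might extend the point to the ANOVA and chi-square tests in 2.3.9. The text does not support that. Section 2.4.8 imports the analysis of incidence. The ANOVA is described for season, playing position and division, with no stated unit of analysis, and on team-level rates it would respect clustering. The chi-square and Fisher tests are for categorical injury descriptors. Neither is clearly the comparison between arms.

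**Conclusion.** The point holds for the between-arm comparison of injury incidence as sections 2.4.8 and 2.3.9 describe it. Followed as written, that test is anti-conservative whenever injury rates vary between teams. The error would be about 11% to 26% in place of 5% over inflations of 1.5 to 3, and 17% if the plan's own 2 carries over to rates. This rests on a two-sided test, a simple Poisson variance, and no adjustment in Appendix J. The size is uncertain within that range; the direction is not.

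The division comparison of incidence (14 against 19 teams) uses the same method and has the same weakness. It is observational, the plan gives no design effect for it, and no size is claimed here.

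**What to change.** In 2.4.8, replace the z-test for the between-arm incidence comparison with one prespecified cluster-level analysis, either:

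- a t-test on team-level log injury rates, each team in its allocated arm, with 17 degrees of freedom if all 19 teams contribute (section 2.4.4.1 lets teams leave or join, so state the rule as number of teams minus 2, and say how a team with no injuries is handled); or
- a Poisson or negative-binomial model with log exposure hours as offset, a team random effect or GEE, and a small-sample correction suited to about 19 clusters.

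Report the rate ratio with the interval from that analysis. Allow for team clustering in the division comparison of incidence as well. If Appendix J already specifies a cluster adjustment, bring 2.3.9 and 2.4.8 into line with it.

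No new data are needed, since injuries and exposure are already to be recorded by team. The cost is a rewording, slightly more analysis work (more for the model than for the t-test), and wider intervals, which reflect the information that 19 teams provide.
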